## Abstract

**Background: **Tongue tumors show intra and inter-tumoral heterogenicity with high incidence, relapse and mortality rates necessitating further research.  Recurrence/metastasis that occurs  after surgical resection of primary cancer is often the reason for poor survival in these patients.  Lymph nodes are the most common site of metastasis in tongue tumors. Therefore, premetastatic molecular changes can be best evaluated in lymph nodes which may epitomize the earliest events in the metastasis cascades. The presence of circulating tumor cells(CTCs) in the absence of nodal disease (N0) may represent tumor aggressiveness, suggesting an immune escape which may have high metastatic potential. This trial  was developed  to investigate the earliest pre-metastatic changes which may regulate tumor dormancy and predict metastasis. A better understanding of organotropism or pre-metastatic changes can help in theragnostic, thereby  preventing the outbreak of overt metastasis.

**Methods:** A single-institutional prospective observational cohort study. This trial will be conducted at a tertiary care Centre (Amrita Institute of Medical Sciences Kochi).  Eligible patients will be enrolled after obtaining informed consent. The dissected lymph nodes will  be subjected to histopathological and immunohistochemical analyses for premetastatic niche (PMN) formation. In addition, circulating tumor cells will be evaluated before treatment and 6 months after treatment. The patients will be followed  up for a period of two years to correlate the findings with the recurrence-free survival.

**Expected results:**  The pre-metastatic changes, if detected will  be  a predictive biomarker. It may help to define future drug targets for metastasis chemoprevention   . CTCs may  define the tumor aggressiveness ,there by  prognostication  and helps in better disease management.

**Ethics and dissemination:** The study has received the following approval:

Ethics Committee of Amrita School of Medicine (ECASM-AIMS-2022-048).Trial Registered Prospectively( CTRI/2022/03/041256 ) on 22/03/2022 under Clinical Trial Registry of India

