### Study implementation/methodology

Patient inclusion is done based on the inclusion criteria. The trial will enroll 97 eligible patients. After obtaining written informed consent, blood samples and tissue biopsy blocks will be collected from them.

For CTC/CTM evaluation – Blood samples with minimum trauma will be collected before and 6 months after surgery. 5 mL of peripheral whole blood samples will be collected in 10-mL vacutainer tubes (Becton Dickinson, New Jersey). The blood samples will be stored in the refrigerator at 2 to 8
^0^ C. CTCs will be isolated by using Drugs Controller General of India (DCGI) approved OncoDiscover liquid biopsy technology. The OncoDiscover CTC isolation technique uses multifunctional, iron oxide-based, magneto-polymeric, and anti-epithelial cell adhesion molecule (EpCAM) targeting superparamagnetic nanoparticles.
^
10
^ Enumeration of CTC is based on CD45-, EpCAM+ and CK8,CK18 &CK19+ expression. CTM clusters are a group of two or more aggregated CTCs. The number of CTCs positive for PD-L1 expression is also evaluated.

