### Primary outcomes

•The correlation of molecular expression of STAT 3, LOX 2, and VEGF in the premetastatic nodes (-ve N) with recurrence -free survival. These markers will be correlated individually. This will allow us to analyse the significance of premetastatic niche formation and the pathways leading to it.•To correlate the presence of CTC/CTM at two different time points to recurrence-free survival. This will allow us to establish the role of liquid biopsy in prognostication ie. the presence of CTC as a predictor/indicator of tumor spread via blood or lymphatic channels.•The evaluation of Stat3 expression in tissue and PD- L1 in CTC will reveal on the local and systemic immune status of patients respectively. Those PD-L -1positive CTCs may be a strong indicator of those exceptional CTCs that escape the immune surveillance mechanism.

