### Participation timeline

All subjects will be part of the trial for two years post initiation of the treatment or till the time when they show progressive incurable disease.

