### Statistical analysis plan

*Sample size calculation*

The sample size is determined by the formula,

n=(Z1−α22)pqd2
, z = Co-efficient of significance (1.96), α = Level of significance (5.0%),

p
= Prevalence of oral tongue tumour (50.0%)

q
 = 1-

p
 (50.0%), d = Desired precision (10.0%).

The minimum sample size for the study is computed and found to be 97 patients.

*Statistical method*

Chi-square Test to test the statistical significance of the association of the molecular expression (severity) of antibodies in lymph nodes and circulating tumor cells as numbers in oral tongue squamous cell carcinoma patients. To find the survival probability of disease-free survival, Kaplan Meier analysis and the comparison will be done using a log-rank test.

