## Discussion

Metastasis can even occur many years after surgical resection of primary cancer due to tumor dormancy. Subramaniam N et al
^
5
^ on a study of OTSCC show 20-30% recurrence within 12 months and 40-50% mortality within 5year even after guideline-based treatment. This study showed younger patients had a higher incidence of tongue tumours with increased adverse pathological features.
^
5
^

In the study by Mizrachi et al. 15% of cN0 oral cancer patients developed neck recurrence.
^
6
^ Blatt et al. in their study on tumor recurrence among OSCC, which is one of the largest retrospective studies on oral squamous cell carcinoma described that recurrence is very frequent especially in the first six months after primary tumor diagnosis, they reported approximately 64% with local recurrences.
^
7
^

The new paradigms of metastatic biology research signify that metastasis is not a late onset event in tumor development nor related to tumor volume. Although progress has been made in understanding the mechanism of cancer spread, the complexity of the metastatic process remains a stumbling block.
^
8
^ Cancer cells are dynamic, with greater plasticity and can build their own niches.
^
8
^
^,^
^
9
^ Each cancer cell must be viewed as an organism capable of developing an entire tumour.
^
8
^ Metastasis is a process in which genetic instability of the primary tumor fuels cell heterogeneity, permitting cloning of a few metastatic cells that ultimately emerge and spread the tumour.
^
9
^
^–^
^
11
^

Tumor metastasis is now believed to be closely pursued by prometastatic milieu, premetastatic niche and metastatic niche formation.
^
12
^ Premetastatic niche is an area devoid of tumour cells, but it can nurture cancer cells. It provides a favourable microenvironment for tumour invasion, endurance and/or proliferation of malignant cells later to develop into metastasis.
^
13
^

These are noncancerous changes in a tumor-free organ and may be the most primitive suggestion of metastasis. Lymph nodes have been suggested to offer fertile soil for cancer cell seeding, proliferation, and metastasis.
^
14
^ These act as crucial metastatic spots and are a decisive prognostic parameter in diverse tumor types.
^
15
^
^,^
^
16
^

Primary tumor initiates the sentinel lymph node remodelling by releasing extracellular vesicles, soluble factors, a variety of cytokines, and growth factors before metastasis spread.
^
11
^
^,^
^
17
^

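### The 6-month CTC/CTM result is set against recurrence-free survival with no landmark or time-dependent handling, so recurrences before the draw can enter a comparison meant to show prediction

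*Protocol article*

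**What the plan says.** Under Primary outcomes, the protocol article sets out "To correlate the presence of CTC/CTM at two different time points to recurrence-free survival". The stated purpose is to establish "the presence of CTC as a predictor/indicator of tumor spread via blood or lymphatic channels". Study implementation/methodology fixes the two draws: "Blood samples with minimum trauma will be collected before and 6 months after surgery". The Abstract describes the same schedule as "circulating tumor cells will be evaluated before treatment and 6 months after treatment".

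The Statistical analysis plan section has a chi-square test for association, and for time-to-event data one sentence: "To find the survival probability of disease-free survival, Kaplan Meier analysis and the comparison will be done using a log-rank test". It does not name the groups compared, the time origin, or who is at risk in an analysis by the 6-month result.

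Three other places bear on the point:
- The section on immunohistochemistry evaluation schedules visits every 2 months in the first year and determines RFS at the end of two years of follow-up.
- Participation timeline keeps patients in the study for "two years post initiation of the treatment or till the time when they show progressive incurable disease".
- The Discussion says that "recurrence is very frequent especially in the first six months after primary tumor diagnosis" and cites 20-30% recurrence within 12 months in oral tongue cancer.

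**The concern.** The 6-month CTC/CTM result is known only at month 6. If RFS is counted from surgery or start of treatment, grouping patients by that result uses information from after some of the events it is meant to predict. Two different errors can follow, depending on who gives the second sample.

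- **Early recurrers are sampled.** Their group is set by blood taken after the event. If recurrence itself raises CTC positivity, early events collect in the CTC-positive group and the marker looks prognostic even when it carries no information about later recurrence.
- **Early recurrers are not sampled.** They drop out of the analysis. Everyone left was event-free for 6 months by construction, so RFS counted from surgery is too high in both groups, although the comparison between groups is not distorted.

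The first case is plausible here. Visits every 2 months will detect recurrences before the draw, and the participation rule does not remove a patient whose early recurrence is still treatable. What is at stake is whether the 6-month result can be read as a predictor.

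**Working it through.** **The plan's own figure.** The sample size formula gives 1.96² × 0.5 × 0.5 / 0.10² = 96.04, rounded up to 97. This reproduces the stated number. It is a precision calculation for a proportion and has no bearing on this point beyond supplying n = 97.

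**Step 1. How many recurrences precede the draw.** Input from the Discussion: recurrence r by 12 months of 20-30%. Assumption: constant hazard. Then S(6) = (1 − r)^0.5 and S(24) = (1 − r)².

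| r at 12 months | Recur before month 6 | Of 97 | Share of 24-month events | Still event-free at month 6 | Events in months 6-24 |
|---|---|---|---|---|---|
| 20% | 10.6% | 10 | 29% | 87 | 25 |
| 25% | 13.4% | 13 | 31% | 84 | 29 |
| 30% | 16.3% | 16 | 32% | 81 | 34 |

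The Discussion describes recurrence as concentrated early (dated from diagnosis). If so, the numbers before the draw would be higher.

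**Step 2. False-positive rate with a null marker, early-loaded recurrence.** Assumptions, none of them in the article except that the 12-month value lies inside the cited range: recurrence 15%, 25% and 35% by 6, 12 and 24 months; CTC positivity 20% in patients recurrence-free at month 6; no relation between the 6-month CTC result and later recurrence. Trials of n = 97 were simulated, with a log-rank test from surgery on all sampled patients at two-sided 5%. Ranges are across independent runs.

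| Early recurrers sampled | Positivity after recurrence 60% | 40% | 30% |
|---|---|---|---|
| 70% | 41-42% | 16-18% | 7-10% |
| 30% | 17-18% | 9-10% | 6-7% |
| 0% | about 5% | about 5% | about 5% |

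At 70% sampled, the apparent rate ratios are about 1.95, 1.4 and 1.2, where the truth is 1. A landmark log-rank from month 6 on the same data rejects in about 4-5% of trials.

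**Step 3. Same question under constant hazard.** Here r = 20-30% at 12 months, positivity in recurrence-free patients is 30%, and all early recurrers are sampled.

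| Positivity after recurrence | False-positive rate | Rate ratio |
|---|---|---|
| 30% (no rise) | about 5% | about 1.0 |
| 50% | 14-18% | about 1.3 |
| 70% | 31-42% | about 1.65 |
| 90% | 57-74% | about 2.0-2.1 |

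With half of early recurrers sampled, the last three rows together span 8-34%. With none sampled, the rate stays near nominal (about 4-7%, within simulation noise). The landmark analysis gives about 4-7% and a rate ratio of about 1.0 throughout.

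**Step 4. Guarantee time if no early recurrer is sampled.** Apparent 24-month RFS from surgery = S(24)/S(6). With the Step 2 inputs this is 0.65/0.85 = 76%, against a true 65%. Under constant hazard, 64% becomes 72%, 56% becomes 65%, and 49% becomes 59%.

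**The case against.** The best counter-argument is that the faulty analysis is inferred. A reader might take the plan to say that one log-rank test, from one time origin, is applied to both draws. It does not say so. The Statistical analysis plan section ties Kaplan-Meier and log-rank to disease-free survival without naming groups, mentions CTC numbers only with the chi-square test, and defines no time origin. An article may also leave such detail to a fuller plan. This limits how firmly the error can be asserted, but it does not remove it. The article itself states the outcome, the draw times and the only survival method, and on the natural reading those do not combine validly for the 6-month sample.

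A second objection is that the size is not established. This stands. The article gives neither the share of early recurrers who will be sampled nor how CTC positivity changes with recurrence. The range therefore includes no bias at all, and the two errors trade off against each other.

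Third, a reader might infer from the Abstract and the Methods that the draw date is contradictory for patients having adjuvant therapy. The article never mentions adjuvant therapy and names surgery as the primary modality, so after treatment may simply mean after surgery. This is a wording point.

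Finally, the article concedes under Methodological issues that sparse CTC sampling limits what can be said about timing, and the word indicator could cover concurrent detection. That tempers the claim but does not supply a valid 6-month analysis. The Introduction also lists CTC/CTM as a secondary objective in N0 patients, whereas Primary outcomes lists it as primary.

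**Conclusion.** The point holds for the 6-month sample only. The pre-operative CTC/CTM analysis and the lymph-node marker analyses are unaffected.

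As written, with RFS running from surgery or treatment, about 10-16 of 97 patients would recur before the draw (20-30% at 12 months, constant hazard). Under the early-loaded assumptions, the false-positive rate for an uninformative marker runs from the nominal 5% to about 40% (70% of early recurrers sampled, positivity 60% versus 20%). More extreme inputs give more. A reader might take 40% as the expected error rate, but the article does not support that, because it rests on sampling and positivity rates the article does not give. If no early recurrers are sampled, the group comparison is sound, but absolute RFS from surgery is overstated by roughly 8-11 percentage points in the cases worked.

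Either way, the 6-month analysis needs its risk set and time origin stated.

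**What to change.** For the 6-month sample, pre-specify a landmark analysis: include only patients alive, recurrence-free and sampled at the draw, start the RFS clock at each patient's draw date, and compare CTC/CTM groups from there. A Cox model with CTC as a time-dependent covariate from the draw date is an acceptable alternative. Report CTC findings in patients who have already recurred as concurrent detection only. Keep the pre-operative sample on RFS from surgery. Make the wording of the second draw time the same in the Abstract and in Study implementation/methodology.

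This changes wording only, provided draw and recurrence dates are recorded. With 27 patients recruited at the time of the article, it could be fixed early. The cost is precision: events before the draw no longer count for the 6-month question, which leaves about 81-87 patients and 25-34 events under the Step 1 assumptions, before any missed samples.

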### Secondary outcomes

•The molecular markers for PMN will be compared in N0 and N+/N++ patients. This may allow a better understanding of the pathways of PMN formation. We expect to see the PMN changes be more prominent in the -ve N samples of N+/N++ patients.•Any architectural histopathologic feature which correlates with the PMN changes if identified will also help as a predictive marker.•To identify the role of CTC to predict PMN formation.

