### Rationale of study

Tongue tumors are a matter of concern for oncologists, researchers and public health policymakers. Patients with tongue tumors have a higher proportion of treatment failures, even after standard treatment protocols. Treatment and clinical decisions on N0 neck in the early stages are still challenging. The primary goal is to investigate the early pre metastatic alterations even before a detectable metastasis and its association in initiating metastasis.

This study may help in
•Elucidating molecular metastatic driving events before or during early stages of metastatic colonization.•Identifying definite lymph node architecture parameters in predicting metastasis before tumor cells arrive.•Studying the significance of CTC/CTM occurring at early nodal-free tumors.

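### The secondary outcome would let a nodal architectural feature count as predictive because it correlates with the premetastatic-niche stains, although no listed outcome compares architecture with recurrence

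*Protocol article*

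**What the plan says.** The second item under Secondary outcomes reads: "Any architectural histopathologic feature which correlates with the PMN changes if identified will also help as a predictive marker". Neither recurrence nor survival appears in that condition.

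The Rationale of study lists among the hoped-for contributions: "Identifying definite lymph node architecture parameters in predicting metastasis before tumor cells arrive". That aim is a clinical one.

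The first item under Primary outcomes is "The correlation of molecular expression of STAT 3, LOX 2, and VEGF in the premetastatic nodes (-ve N) with recurrence -free survival". The second ties CTC/CTM to the same endpoint. Architecture is in neither.

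The Statistical analysis plan section specifies a "Chi-square Test to test the statistical significance of the association of the molecular expression (severity) of antibodies in lymph nodes and circulating tumor cells" and, for disease-free survival, "Kaplan Meier analysis and the comparison will be done using a log-rank test". It names no architectural variable, and it does not say which groups the log-rank test compares.

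The Abstract says that nodes will have histopathological and immunohistochemical analyses and that patients are followed "to correlate the findings with the recurrence-free survival". Its expected results begin "The pre-metastatic changes, if detected will" and go on to describe those changes as a predictive biomarker.

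**The concern.** The architectural feature is to be judged against a marker that has not itself been shown to matter. If STAT 3, LOX 2 and VEGF staining turn out to be unrelated to recurrence, a feature that tracks the staining would still meet the stated condition. If the stains are prognostic, a feature correlated with them may still carry little or no information on recurrence, because correlation does not pass along a chain.

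At stake is how a secondary finding is labelled. A reader of the results could take a routine-histology feature to be a predictor of metastasis when it had only been compared with stains on the same nodes. The aim in the rationale would then seem to have been met without having been examined.

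**Working it through.** **The plan's own figure.** The Statistical analysis plan gives z = 1.96, p = q = 0.50 and d = 0.10. Then n = z²pq/d² = 1.96² × 0.25 / 0.01 = 96.04, rounded up to 97. The stated 97 is reproduced. It is used below only as the number of patients.

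**Aim against outcome.**

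| Section | What architecture is related to |
|---|---|
| Rationale of study | metastasis |
| Primary outcomes | not mentioned (stains and CTC/CTM against recurrence-free survival) |
| Secondary outcomes | PMN changes |
| Statistical analysis plan | not mentioned |
| Abstract | unspecified findings against recurrence-free survival |

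No listed outcome measures the aim in the rationale.

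**How easily the stated condition is met.** At the two-sided 5% level with 97 patients (95 degrees of freedom), the critical correlation is t/√(95 + t²) = 0.20. A modest correlation suffices.

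**What the condition says about recurrence.** The document gives no effect sizes, so these are assumptions. Take correlations of 0.5 (feature with stain) and 0.3 (stain with outcome). If the feature acts only through the stain, its correlation with outcome is 0.5 × 0.3 = 0.15, which is below 0.20. Without that restriction, the algebra allows 0.15 ± √(0.75 × 0.91) = 0.15 ± 0.826, that is, -0.68 to +0.98. With 0.7 and 0.5 it allows 0.35 ± √(0.51 × 0.75), that is, -0.27 to +0.97. These are limits of the possible, not likely values. They show only that a zero or reversed relation is not excluded.

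**The same point with proportions.** Assume 97 patients split evenly by feature (48.5 each), PMN positivity of 70% with the feature and 30% without, and recurrence as a simple proportion. The 20% base is the lower end of the 20-30% at 12 months cited in the Discussion and is used for illustration.

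- Feature against PMN, 70% versus 30%: power 98.5%.
- If PMN does not affect recurrence (20% in both groups), recurrence by feature is also 20% in both groups, yet the condition is almost certain to be met.
- If PMN raises recurrence from 20% to 40% and the feature acts only through PMN, recurrence is 0.7 × 40% + 0.3 × 20% = 34% with the feature and 0.3 × 40% + 0.7 × 20% = 26% without. Power to show that difference is about 13%.
- With PMN positivity from 65%/35% to 80%/20% and recurrence from 30%/20% to 50%/20%, power is 85% to nearly 100% for feature against PMN, and 5% to 46% for feature against recurrence.

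**The case against.** The wording is aspirational. It says that a feature, if found, will help, and it sets no test or threshold. It is therefore not a formal decision rule, and a reader should not infer that the trial has committed itself to announcing a predictor. This stands and keeps the point modest.

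The object of prediction is unstated. The next item under Secondary outcomes speaks of CTC predicting PMN formation, and on that reading correlation with PMN would be the right criterion. The word *also* may further presuppose that the stains first prove prognostic. Neither reading is written out, and the rationale names metastasis. The ambiguity is itself a reason to reword.

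The Abstract's sentence about correlating the findings with recurrence-free survival can be read to include histopathology, and the log-rank comparison does not exclude it. So it would be too strong to infer that architecture will never be tested against a clinical outcome. But the sentence is general, no outcome carries it through, and the secondary outcome states a different criterion.

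A reader might also attach a false-positive rate. Five features against three stains make 15 tests, and 1 - 0.95^15 = 54%. The documents do not support that as an expected size. They give no count of features, and the section on antibody selection links STAT3 activation to VEGF expression, so the tests are not independent.

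Nor are the data already in hand. Study status reports 27 patients recruited and evaluation of the nodes still to come. The article describes no scoring of architecture, and the blinded double reading is set out after the staining steps. However, the existing secondary outcome already presupposes that architecture is read on these nodes, and recurrence-free survival is to be determined at two years, so the direct comparison adds no new procedure.

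Finally, the direct comparison has low power. That stands as a cost. It is not a reason to let an easier association with an unproven marker take its place.

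**Conclusion.** The point holds as a mismatch between aim and criterion. As worded, the secondary outcome would allow an architectural feature to be called predictive on correlation with PMN changes alone, while the link from those changes to recurrence is still the primary question and no listed outcome compares architecture with recurrence.

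The conclusion rests on the wording and on correlation not being transitive; it does not depend on any particular effect size. The correlation range and the power figures are illustrations under assumed inputs and do not estimate how often a feature would be mislabelled. The item is an open-ended secondary outcome and touches neither the sample size nor the primary analyses. The change is a worthwhile, low-cost improvement.

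**What to change.** Reword the second secondary outcome so that architectural features assessed on these nodes are compared directly with recurrence-free survival. Use the Kaplan-Meier and log-rank methods that the Statistical analysis plan already names (there for disease-free survival). State how many features were examined, give the estimate with its uncertainty, and label the analysis exploratory.

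Report correlation with STAT 3, LOX 2 and VEGF A as supportive or hypothesis-generating. Do not call a feature predictive of metastasis on that correlation alone; in a single observational cohort *prognostic* is the apter word in any case.

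The cost is a change of wording and a few analyses on node readings and follow-up that are already planned. The downside is low power with 97 patients: a real feature may stay unconfirmed, and the report should say so.
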